## Abstract

**Background:**

Barriers to depression treatment among Hispanic populations include persistent stigma, inadequate doctor patient communication (DPC) and resultant sub-optimal use of anti-depressant medications. Stigma is primarily perpetuated due to inadequate disease literacy and cultural factors. Common concerns about depression treatments among Hispanics include fears about the addictive and harmful properties of antidepressants, worries about taking too many pills, and the stigma attached to taking psychotropic medications. The current manuscript presents the study protocol for the Depression Screening and Education: Options to Reduce Barriers to Treatment (DESEO) study funded by the Center for Medicare and Medicaid Services (CMS) Grants to Support the Hispanic Health Services Research Grant Program.

**Methods/Design:**

DESEO will implement universal screening with a self-report depression screening tool (the 9-item Patient Health Questionnaire (PHQ-9)) that is presented through a customized web application and a Depression Education Intervention (DEI) designed to increase disease literacy, and dispel myths about depression and its treatment among Hispanic patients thus reducing stigma and increasing treatment engagement. This project will be conducted at one community health center whose patient population is majority Hispanic. The target enrollment for recruitment is 350 patients over the 24-month study period. A one-group, pretest-posttest design will be used to asses knowledge of depression and its treatment and related stigma before, immediately after, and one month post intervention.

**Discussion:**

Primary care settings often are the gateway to identifying undiagnosed mental health disorders, particularly for people with comorbid physical health conditions. This study is unique in that it aims to examine the specific role of patient education as an intervention to increase engagement in depression treatment. By participating in the DEI, it is expected that patients will have time to understand treatment options, participate in shared decision-making with their provider, and increase engagement in treatment of depression which might lead to improved overall health. It is also expected that implementation of the iPad Depression Screening application will increase provider awareness of the incidence and prevalence of depression in their own practice and improve the performance and care the clinic provides.

**Trial registration:**

The study was registered with: NCT02491034 July 2, 2015.

## Background

### Hispanics and depression

Clinical depression is the leading cause of medical disability, health burden, and increased medical cost in the United States and the world, costing an estimated $ 83–125 billion in the U.S. each year, and more than half these expenses are publicly funded [1]. It is estimated that the lifetime prevalence of a psychiatric disorder for Hispanics residing in the United States is 28.1 % for men and 30.2 % for women. Hispanics are more likely to experience a psychiatric disorder if they are born in the United States, are proficient in the English language, or are third-generation in the United States [2]. Hispanics have a higher prevalence of diabetes but also have double the risk of comorbid depression than the general population, with rates as high as 33 % [3].

For many Hispanics, response to depression treatment may require a considerable amount of time to reach remission, as much as two and a half years [4] Additionally, relapse rates are high and the slow response to treatment may explain the premature discontinuation of medication by patients. Intractable symptoms and slow recovery leave minority populations with a considerable disease burden for a substantial length of time compared to non-Latino whites [4, 5].

Low use of anti-depressant medication, poor doctor patient communication, and persistent stigma around issues of mental illness are key barriers to the treatment of depression in Hispanic populations [4, 6, 7]. Hispanics initiate anti-depressant medication treatment at a much lower rate than whites, and are more likely to discontinue their treatment for depression without consulting their physician, in spite of being equally likely as whites to have received a medication prescription from their primary care provider [8]. Common concerns about depression treatments include fears about the addictive and harmful properties of antidepressants, worries about taking too many pills, and the stigma attached to taking psychotropic medications [9, 10]. Somatic presentation of depressive symptoms, especially in the context of comorbid illness, impedes accurate and timely detection by primary care providers and, in settings where systematic screening for depression is absent, barriers to treatment are further amplified [11].

### Primary care

By 2003, 54 % of people with mental health disorders were served in primary care, without referral to specialty mental health [12], supporting the description of primary care as the ‘de facto’ mental health care system [13]. Hispanics, in particular, are more likely to receive mental health care in primary care settings [14]. Many reasons have been cited for this trend, from lack of access to mental health specialists, income and insurance barriers, to the trust of the relationship with the family physician [15, 16]. Additionally, low English proficiency is associated with reports of poor quality of primary care, an absence of a source of care, and a lack of continuity [17]. Other studies conclude that treatment and linguistic barriers are likely to be even more pronounced at the community level for Hispanics [18–21].

### Importance of screening

Self-report depression screening instruments can save provider time, minimize stigma, and engage patients in the identification of their symptoms of depression. Screening instruments can be powerful tools in assisting primary care providers with detecting depression in their patient population, diagnosing depression and monitoring treatment response. These instruments can also help track a patient’s overall depression severity as well as the specific symptoms that are improving or not with treatment [22]. The most recent recommendations from the U.S. Preventive Services Task Force are that primary care providers screen adult patients for depression only if systems are in place to ensure treatment and follow-up [23].

### Role of education

Management of depression among Hispanics in community-based safety net settings is confounded by issues of disease literacy, cultural treatment preferences and financial barriers to care [24, 25]. The role of patient education in management of chronic disease to increase patient engagement and improve health outcomes has been well established [26]. However, less is known about patient education and its role in mental illness [27]. Depression education interventions, which focus on symptom recognition, stress reduction techniques, and behavioral activation to reduce barriers to treatment, show promise [28, 29].

Educational interventions to proactively address barriers to depression treatment for Hispanic patients have included adapting materials for literacy and cultural content, reimbursing patients for completing outcome measures, and covering transportation expenses. Additional strategies include offering the patients the opportunity to include family members in sessions, if preferred, with a particular focus on linking patient education to depression self-management and socioeconomic stressors created by their illness. Provision of patient education and homework materials that are linguistically, idiomatically, and literacy-level appropriate is key [30].

### Aims

The current paper provides a description of the design of DESEO: Depression Screening and Education: Options to Reduce Barriers to Treatment. The primary aim of DESEO is to implement a Depression Education Intervention (DEI) designed to increase disease literacy, and dispel myths about depression and its treatment among Hispanic patients thus reducing stigma and increasing treatment engagement. The secondary aim of the study is to test the feasibility of universal screening for depression utilizing the 9-item Patient Health Questionnaire (PHQ-9) [31] via the iPad Depression Screening application.

### Objectives

To increase knowledge of depression (signs/symptoms, causes, risk factors, treatment, cultural beliefs, and its role in chronic disease) among Hispanics in a primary care setting.To reduce perceived cultural stigma about depression and its treatment through a culturally and linguistically appropriate educational intervention.To increase engagement in depression treatment in primary care by Hispanic patients.To systematically screen all adult primary care patients with an iPad Depression Screening application.To increase provider detection of depression in patients through the proper use and interpretation of the PHQ-9.

### Hypotheses

Our hypothesis is that the provision of depression education to Hispanic patients in a community based health center will lead to an increase in the understanding of depression, a reduction in stigma and an increase in patient engagement in treatment. Additionally, we hypothesize that the implementation of the iPad Depression Screening application will increase provider awareness of the incidence and prevalence of depression in their own practice and thus improve the performance and care the clinic provides.

## Methods/Design

### Setting and participants

The study will take place at one Federally Qualified Health Center that primarily serves a Hispanic population in north Texas and whose mission is to provide a community medical home through accessible, compassionate and quality health care services. The center offers a full range of quality family-oriented comprehensive primary and preventive services, including Family Medicine, Pediatrics, Obstetrics/Gynecology, family planning services, prenatal care, and health education promotion and disease prevention services. In 2013, the clinic had 11,274 unduplicated patients and 25,362 patient visits. Of those patients, 83 % were Hispanic. The majority did not speak English.

The target enrollment for recruitment is 350 patients over the 24-month study period. All adult primary care patients at the clinic will be asked to participate in screening for depression with the iPad Depression Screening application (universal screening). The clinic sees an average of 450–500 unique adult patients per month (new and/or unduplicated) or 100–125 patients per week. It is expected that *at least* 10 % of the patient population will screen positive for depression. Patients that are not Hispanic will be ineligible for the study because the intervention is culturally and linguistically adapted for a Hispanic population. Patients who are already in treatment for depression (medication and/or psychotherapy) will also be excluded since treatment engagement is an expected outcome. The study protocol was reviewed and approved by the Institutional Review Board of the University of Texas at Arlington. All patients will provide written informed consent to participate.

### Study design and intervention

This project will implement universal screening for depression and a Depression Education Intervention (DEI) to increase detection, diagnosis, and treatment of depression at one community health center whose patient population is majority Hispanic. The project will begin with a self-report depression screening tool that is administered to all clinic patients (universal screening) through a customized web application using an iPad. This iPad Depression Screening application technology represents an innovative, evidence-based initiative that is the first of its kind in that it aims to increase access to depression screening for patients in primary care. Through the use of the iPad Depression Screening application, patients will be identified and referred to the Depression Educator. The DEI is designed to increase disease literacy, and dispel myths about depression and its treatment. A one-group pretest-posttest design will be used to asses knowledge of depression and its treatment and related stigma before, immediately after, and one month post education intervention.

#### Universal screening with iPad technology

The first step will involve training primary care providers and designated clinical staff in the use and interpretation of the PHQ-9 and the utilization of the iPad Depression Screening application. All adult primary care patients will be asked to complete the iPad Depression Screening (universal screening) at the annual visit and at new/non-acute visits. Using a brief script, medical assistants (MAs) will give the patient the iPad during the routine intake process (weight, blood pressure, etc.) and ask them to complete the screening for depression. Patients can refuse the depression screening process with no adverse effect to the services they receive at the clinic. The first screen in the iPad application will be used to record consent, and the patient will be informed that refusal to consent for screening will have no effect on the care they receive at the clinic. If the patient does not consent, the screening process will be terminated and the patient will continue with their scheduled visit.

The iPad Depression Screening application begins with the first two screening items of the PHQ-9 (the PHQ-2). The PHQ-2 is a validated “first-step” approach to screen for depression, which indicates if a patient should be further evaluated using the PHQ-9 [32]. For patients with scores above 3 on the first two items, the application automatically expands to the additional 7 items of the PHQ-9. The iPad Depression Screening will be presented in English or Spanish, depending on the patient’s preference. Once completed, an electronic notification is generated to the Depression Educator, the patient’s primary care provider and other designated clinic staff caring for the patient. Upon completion of the screening, the application screen will lock with a message to return the iPad to a clinic staff member.

Immediately after a patient screens positive for depression, the intake nurse will document the PHQ-9 score in the patient’s electronic health record (EHR). A notification will inform the provider that the patient screened positive for depression to enable the provider to interpret the depression score. Patients identified as depressed by the iPad Depression Screening application will be further assessed using the Major Depression Diagnostic Checklist (MDDC), a clinical interview tool used to confirm the nine criteria for depression from the Diagnostic and Statistical Manual of Mental Disorders (DSM-IV) [33]. The provider will then immediately facilitate an introduction to the Depression Educator, a practice known as a warm hand off, which establishes rapport and instills a sense of trust in the patient. Patients who do not meet the diagnostic criteria for depression will be excluded from the study. See Fig. 1 for a summary of the study flow.

**Fig. 1 Fig1:**
[figure not shown]
DESEO Participant Flow

#### Depression Education Intervention (DEI)

Patients identified as depressed by the iPad Depression Screening application (PHQ-9) will be referred to the Depression Educator for potential enrollment in the Depression Education Intervention (DEI). Patients who screen positive for depression but previously had a diagnosis of depression and are in treatment, will be excluded from enrollment in the DEI. The Depression Educator will confirm the diagnosis of major depression using the MDDC, if the provider has not already done so, and that the patient is not currently in treatment for depression or other mood disorder. The Depression Educator will explain the current project, including the compensation for completion of study measures at two sessions: baseline session to consent and enroll, and after completion of the DEI within 2 weeks. The Depression Educator will also explain that there will be one follow-up phone call one month after the completion of the DEI session. The Depression Educator will attempt to build rapport, engage the patient, and invite the patient to participate. If the patient agrees to participate in the DEI, s/he will be guided through the informed consent process. If a patient declines participation, s/he will receive routine care for their depression from the clinic providers.

The Depression Educator will document the patient’s PHQ-9 baseline score and administer the rest of the baseline measures, which includes the Depression Knowledge Measure (DKM) and three stigma measures (see Table 1). All measures will be documented in an electronic, password-protected research database. The Depression Educator will then schedule the patient to return to the clinic for the DEI. The patient will be encouraged to bring family members and loved ones to the session. The patient should be scheduled to return for the DEI within several days, at most within 2 weeks, of the first session.

**Table 1 Tab1:** DESEO study assessments and frequency of administration

Assessment	Purpose	Screening	Baseline	2^nd^ Session (pre or post DEI)	Follow-Up
Patient Health Questionnaire (PHQ-9)	Measure depressive symptoms	X		pre	X
Depression Knowledge Measure (DKM)	Evaluate symptom recognition and treatment knowledge		X	post	X
Stigma Concerns About Mental Health Care (SCMHC)	Assess stigma related barriers to depression treatment utilization		X	post	X
Latino Scale for Antidepressant Stigma (LSAS)	Assess stigma related to the use of antidepressants		X	post	X
Social Distance (SD)	Measures desire for social distance from someone with depression		X	post	X

When the patient returns for the DEI, the Depression Educator will administer the PHQ-9 via the iPad Screening Application prior to the education intervention. The DEI uses a unique, culturally adapted depression *fotonovela* titled “Secret Feelings” developed by Cabassa, Molina and Baron [34]. The *fotonovela* is a popular comic-book style pamphlet that portrays a dramatic story using photographs and dialogue bubbles, which has become an effective tool for engaging Hispanic audiences and increasing knowledge about specific health issues [35, 36]. Using the *fotonovela* as a tool to promote discussion, the DEI is designed to enhance the awareness and understanding of depression, its role in chronic disease, its impact on Hispanic populations and the multitude of barriers to effective treatment. The DEI will be provided in one individual session by the Depression Educator in the presence of support by family members or loved ones, if desired. The DEI will be provided in English or Spanish depending on patient preference, to reduce stigma and enhance the comfort of patients to ask questions and discuss fears. Upon completion of the DEI, the patient will be asked to complete the DKM and the three stigma measures again. The Depression Educator will record the results of the measures and the second PHQ-9 in the research database. See Fig. 1 for study flow, Table 1 for summary of measures.

To determine the effectiveness of the intervention in engaging participant’s in depression treatment, the Depression Educator will call the patient one month after the DEI. The Depression Educator will assess if the patient is currently engaged in depression treatment of any kind (pharmacotherapy, counseling or other behavioral intervention). When possible, the information will be verified with the EHR. The Depression Educator will also administer all measures including the PHQ-9, DKM and three stigma measures (see Table 1).

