### Data monitoring and analysis

The data monitoring will focus on the proper collection of the depression measures, the depression knowledge measure, the stigma measures and patient outcomes after the DEI. A Project Coordinator will be responsible for monitoring the database and provide general support to the Depression Educator concerning issues related to DESEO. Such issues might include identifying problems with implementation, support to clinical staff to insure proper use of the iPad Depression Screening and Monitoring application, and facilitate the proper recording of scores in the EHR. Other duties include maintenance and oversight of the research database, tracking of supplies of depression education materials, and ensure continued fidelity of all clinic staff to the study protocols.

A sample size of 350 would be sufficient to find a statistically significant effect size of d = .176 (α = .05, Power [1-β] = .95). While the study is expected to produce a far greater effect size, a large sample size will provide additional analytic and investigative opportunities surrounding the psychometric properties and validity of the measures. The stigma measures, in particular, have not been tested in a primary care population and are of interest in identifying barriers to mental health treatment for Hispanic populations.

The primary analysis will assess changes in knowledge of depression pre-DEI, post-DEI and one month post-DEI using the Depression Knowledge Measure and changes in cultural attitudes toward depression pre and post DEI using the stigma measures (Table 1). Additional analyses will determine if the DEI leads to engagement in depression treatment for Hispanic patients by quantifying the number of Hispanic patients diagnosed with depression who went on to begin depression treatment after the intervention. Further analysis will quantify which treatment modality the patient with depression chose after the DEI: pharmacotherapy, counseling, or other behavioral intervention based on follow-up phone call one month post intervention and/or information in the EHR.

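### The Depression Educator who delivers the DEI also records the post-DEI scales and collects the one-month measures and engagement, so a rise in desirable answering after the session cannot be told from a DEI effect

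*Protocol article*

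**What the plan says.** The design is uncontrolled: "A one-group pretest-posttest design will be used" (Study design and intervention). The section on the Depression Education Intervention gives one role, the Depression Educator, the following tasks in sequence:

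- building rapport with the patient and inviting participation;
- administering the baseline Depression Knowledge Measure (DKM) and three stigma scales;
- delivering the DEI in a single individual session, with family present if the patient wishes;
- entering the post-DEI DKM, stigma and PHQ-9 results in the research database (who hands the scales to the patient at that point is not named);
- at one month, making the call: "the Depression Educator will call the patient one month after the DEI".

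On that call, "The Depression Educator will assess if the patient is currently engaged in depression treatment of any kind", and the Educator gives the PHQ-9, DKM and stigma scales again. For engagement the safeguard is one sentence: "When possible, the information will be verified with the EHR". In Data monitoring and analysis, the treatment modality chosen is to be determined "based on follow-up phone call one month post intervention and/or information in the EHR".

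**The concern.** The Educator spends a session explaining that stigma is unfounded and that treatment helps. The same role then records the patient's stigma answers, and a month later asks whether the patient has started treatment. A patient who wants to please, or who now knows which answer is welcome, will move in the direction of the study's hypotheses. Without a comparison group nothing cancels this.

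The outcomes concerned are central. Change in knowledge and in stigma is the primary analysis, and the engagement call is how the protocol judges whether the DEI brings patients into treatment. If part of the change is reporting, the study would credit the DEI with it and could not detect the error from its own data.

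**Working it through.** **1. Which outcomes are exposed.** Setting the passages side by side:

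- Stigma scales after the DEI: recorded by the Educator, directly after the session. Exposed.
- Stigma scales at one month: administered by the Educator by telephone. Exposed.
- Engagement at one month: asked by the Educator, verified only where feasible. Exposed wherever verification is not done.
- DKM: scored right or wrong, 0 to 17. A wish to please does not supply correct answers, but prompting can. Less exposed.
- Screening PHQ-9: self-completed on an iPad handed over by medical assistants. Not exposed.
- Second PHQ-9: taken on the iPad before the DEI. Not exposed to pressure that the session creates.
- Screening uptake, new diagnoses and antidepressant treatment: from iPad, clinic or health records. Not exposed.

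**2. What enters the change score.** Let the desirable-answering shift be s0 at baseline and s1 after the DEI. The observed mean change is the true change plus (s1 − s0). Because the Educator also gives the baseline scales, a constant shift (s1 = s0) cancels. Only an increase after the DEI, b = s1 − s0 > 0, biases the result.

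**3. The plan's own figure.** Inputs: N = 350 ("The target enrollment for recruitment is 350 patients over the 24-month study period") and "statistically significant effect size of d = .176 (α = .05, Power [1-β] = .95"). For a paired mean change, n = ((z_alpha + z_power)/d)².

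- One-sided: ((1.645 + 1.645)/0.176)² = 349.4, so 350. This reproduces the plan.
- Two-sided: ((1.960 + 1.645)/0.176)² = 419.5, so 420. This does not; two-sided power at 350 is about 91%.

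The sidedness is not stated, so both are carried below.

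**4. What a pure reporting shift would do at N = 350.** Assume no true effect and a shift of b SD of change. The chance of significance is Φ(b√350 − z_alpha), plus the opposite tail when two-sided. With √350 = 18.71 and b = 0.10: Φ(1.871 − 1.645) = 0.59 one-sided and Φ(1.871 − 1.960) = 0.47 two-sided.

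| Assumed b | One-sided | Two-sided |
|---|---|---|
| 0 | 5% | 5% |
| 0.05 | 24% | 16% |
| 0.10 | 59% | 47% |
| 0.15 | 88% | 80% |
| 0.20 | 98% | 96% |

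The documents give no value for b. The table shows only that a sample sized for a small effect is also sensitive to a small bias.

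**5. Engagement.** If a proportion p is truly in treatment and a fraction f of the rest say yes, the reported rate is p + (1 − p)f. Both inputs are assumed.

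- p = 0.40, f = 0.10: 0.40 + 0.60 × 0.10 = 0.46, or 350 × 0.06 = 21 extra patients.
- p = 0.40, f = 0.20: 0.40 + 0.60 × 0.20 = 0.52, or 42 extra patients.
- Over p = 0.30 to 0.50 and f = 0.05 to 0.20, the inflation runs from 2.5 percentage points (about 9 patients) to 14 points (49 patients).

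These figures apply only where the record check does not correct the answer, and they allow no error in the other direction.

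**The case against.** Much can be said for the plan, and several points stand.

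- A reader might infer that every outcome is compromised. The documents do not support this: the screening PHQ-9, the pre-DEI PHQ-9 and the record-based outcomes do not carry the pressure described, and the DKM is a keyed test.
- The Educator measures at baseline too, so a stable wish to please cancels. This stands; only the increase matters. It does not dispose of the point, because the teaching comes between the two measurements.
- The stigma scales are not equally exposed. The antidepressant-stigma response options refer to what others think, which is less direct self-presentation than the scales on the patient's own concerns or own social distance. This stands.
- A reader might infer from the and/or wording that the engagement count itself mixes sources without a rule. That phrase closes the sentence on treatment modality; the preceding sentence, on how many began treatment, does not contain it. For engagement the text gives the call plus verification where feasible, and the weakness lies in that qualifier.
- A reader might infer that the call can be reassigned at no cost because "A Project Coordinator will be responsible for monitoring the database and provide general support to the Depression Educator". The article gives that role no patient contact and states neither spare capacity nor Spanish fluency, while most clinic patients did not speak English. Reassignment is therefore optional.
- Making the health record the sole measure would redefine an outcome that covers treatment of any kind. Counselling is not among the clinic services listed, and care elsewhere may be missed. This stands, and is why both sources should be shown.
- The uncontrolled design has a larger limit: notifying the provider and confirming the diagnosis could themselves prompt treatment. No change of assessor removes that. It stands, but is no reason to leave an avoidable source of bias in place.

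**Conclusion.** The point holds for the stigma scales and for self-reported engagement, and more weakly, through prompting, for the DKM. The role that delivers the DEI records the results taken just after it and personally collects the one-month answers. With one group, an increase in desirable answering cannot be separated from a DEI effect, and an unverified yes about treatment can count as engagement.

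The likely direction is towards the hypotheses; the size is unknown. The 59% and 47% figures for a 0.10 SD shift, and the 2.5 to 14 point inflation of engagement, rest on assumed inputs. A reader might take them as evidence that the results will be false; they are not estimates and do not show that.

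The protocol does not contradict itself here. It fixes a data-collection arrangement that could be improved cheaply with tools it already uses, and the change should be made.

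**What to change.** **(a) Private self-completion.** Have patients complete the DKM and stigma scales on the iPad already used for the PHQ-9, away from the Educator and family, at both baseline and post-DEI so that the mode stays the same. Where literacy requires it, existing clinic staff not delivering the DEI read the items aloud.

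**(b) Record check for all.** Replace verification where feasible with a check of the health record for every enrolled patient, including those not reached by telephone, noting whether treatment started, when, and which modality. Report record-documented and self-reported engagement side by side, stating that the record can miss care outside the clinic and that self-report may overstate engagement.

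**(c) Optional.** If staff capacity and language allow, someone not delivering the DEI makes the one-month call.

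**Cost.** The scales must be added to the iPad form, and each patient needs one chart check. There is one trade-off. If (a) is adopted without (c), the baseline-to-one-month change compares private self-completion with an interview by the Educator, so a constant shift no longer cancels there. The report should say so. The pre-to-post comparison, which the analysis section names for the stigma scales, is not affected by this.

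### The one-month item records whether the patient is in treatment at the call, so it does not measure the analysed outcome, which is starting treatment after the DEI

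*Protocol article*

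**What the plan says.** All places are in the Methods/Design part of the protocol article.

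- **What is collected** (Depression Education Intervention): to judge whether the intervention engages patients in treatment, the educator telephones one month after the DEI and is to "assess if the patient is currently engaged in depression treatment of any kind (pharmacotherapy, counseling or other behavioral intervention". The answer is checked against the electronic health record (EHR) when that is possible.
- **What is analysed** (Data monitoring and analysis): engagement is determined by "quantifying the number of Hispanic patients diagnosed with depression who went on to begin depression treatment after the intervention". A further analysis of the type of treatment chosen draws on the call, the EHR or both.
- **When untreated status is checked** (Depression Education Intervention): at eligibility, the educator confirms "that the patient is not currently in treatment for depression or other mood disorder".
- **When the DEI takes place** (same section): at a separate visit, to be scheduled "within several days, at most within 2 weeks, of the first session". Before the DEI at that visit the text describes the PHQ-9 and no second check of treatment status.
- **What the provider knows by then** (Universal screening with iPad technology): "A notification will inform the provider that the patient screened positive for depression".

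**The concern.** The article states both the item and the outcome, and they do not match. The item is a status at one time point. The outcome is an event, a first start, that has to fall after the DEI. They agree only if nobody starts treatment between the eligibility check and the DEI, and nobody who starts after the DEI has stopped by the call.

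The design leaves room for both. The provider is aware of the positive screen before the DEI, the gap can reach 2 weeks, and no passage says that treatment waits for the DEI. The article also plans, separately, to examine whether the screening application changes how providers diagnose and treat depression. It thus allows that screening alone may lead to treatment. Without start dates, one and the same start could support both the screening claim and the DEI claim.

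At stake is the engagement result. Engagement belongs to the primary aim, the objectives and the hypothesis, although the analysis section lists it among additional analyses. The knowledge and stigma results and the sample size are not affected.

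**Working it through.** **The plan's own figure.** The article gives no figure for engagement. Its only calculation is 350 patients for d = 0.176, α = 0.05, power 0.95. As a one-sample mean change this is ((1.645 + 1.645)/0.176)² = 349.4, rounded up to 350, with one-sided α. Two-sided α would need 420. It concerns a mean change score, and nothing below depends on it except the use of 350 as the number of patients.

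**What the call item returns, by treatment history**

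| Treatment history | Item at the call | Start after the DEI? |
|---|---|---|
| Starts in the gap, still treated at the call | yes | no |
| Starts in the gap, stops before the call | no | no |
| Starts after the DEI, still treated at the call | yes | yes |
| Starts after the DEI, stops before the call | no | yes |
| Never starts | no | no |

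The first row is wrongly counted and the fourth is wrongly missed.

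**Illustration of the first error.** All rates are assumptions; the article gives none. Let q be the share of enrolled patients who start between enrolment and the DEI, and p the share of the rest who start between the DEI and the call. Assume 350 patients, no loss to follow-up and nobody stopping.

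- Counted by the item: 350 × (q + (1 − q)p)
- True post-DEI starts: 350 × (1 − q)p
- Excess: 350 × q
- Share of those counted that predates the DEI: q / (q + (1 − q)p)

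With p = 0.30:

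| q | Counted | Post-DEI starts | Excess | Share predating the DEI |
|---|---|---|---|---|
| 0 | 105 | 105 | 0 | 0% |
| 0.05 | 117.25 (33.5%) | 99.75 | 17.5 | 0.05/0.335 = 15% |
| 0.10 | 129.5 (37%) | 94.5 | 35 | 0.10/0.37 = 27% |
| 0.20 | 154 (44%) | 84 | 70 | 0.20/0.44 = 45% |

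The share depends on p as well. With q = 0.10 it is 0.10/0.19 = 53% at p = 0.10 and 0.10/0.55 = 18% at p = 0.50.

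**The opposite error.** Let s be the share of post-DEI starters who have stopped by the call, with gap starters all still in treatment. The item then misses 350 × (1 − q)p × s patients. The two errors cancel in the total when s = q / ((1 − q)p). With q = 0.10 and p = 0.30 this is 0.10/0.27 = 37%; with q = 0.05 it is 0.05/0.285 = 18%. Above that value the item undercounts post-DEI starts. Even when the totals agree, the wrong patients are counted.

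**The case against.** The strongest objection is that the analysis section already defines the outcome as a start after the intervention, which excludes earlier starts. A reader might infer that the plan sets out to credit earlier starts to the DEI. The documents do not support that. The stated intention is right, and the fault is that the described item cannot deliver it.

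Second, the EHR could date some starts, and an article commonly leaves derivation rules to the full protocol or analysis plan. This stands in part. But the EHR is described only as a check on the call where possible, or as one of two sources for the type of treatment. Counseling or behavioral treatment obtained elsewhere may not appear in it. An analysis plan cannot recover a start date that was never collected.

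Third, Table 1 shows no treatment item at the second session. That is no evidence either way: the table lists scales, and it shows no treatment item at follow-up either, where the text plainly collects one.

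Fourth, a reader might infer that a large part of the count would be treatment begun at the screening visit itself. The documents do not support that. The educator checks for current treatment after the provider's handoff, which would screen out at least some such starts. Applying one constant daily start rate before and after the DEI would not settle the size either, because it assumes that the DEI has no effect on starting.

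Fifth, a reader might infer that the engagement rate is necessarily inflated. It is not: starts that stop before the call work the other way.

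Last, with one group and no control, even correctly dated starts cannot be separated from the effect of screening, diagnosis and routine care. That stands. It limits what the fix achieves, but temporal order is the least that the engagement claim needs.

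**Conclusion.** The point holds as a mismatch between measurement and outcome. Following the described item does not yield the described count. Patients who start in the gap and remain in treatment are indistinguishable from post-DEI starters, and those who start after the DEI and stop before the call are lost.

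Size and net direction cannot be determined from the article. The first error is zero if nobody starts in the gap. The 15-45% shown above rests on assumed values (5-20% starting before the DEI, 30% of the rest after it, no stopping and no loss to follow-up) and is not an estimate for this trial.

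Severity is moderate. Engagement is part of the primary aim but is analysed as an additional, uncontrolled count, and the primary knowledge and stigma analyses do not depend on it.

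**What to change.** Measurement and definition only; nothing in patient care changes.

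1. At the second session, before the DEI, ask whether the patient has started any depression treatment since enrolment, and when. The PHQ-9 is already taken at that point.
2. At the one-month call, besides current status, ask about any treatment since the DEI and its start date. Supplement with EHR dates where available.
3. Define engagement as a first treatment start after the DEI and up to the call, among patients still untreated at the DEI.
4. Report starts before the DEI, and being in treatment at the call, as separate results. Keep gap starters in the knowledge and stigma analyses.

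The cost is one or two extra questions at contacts that already take place, and a somewhat smaller numerator and denominator. In the illustration with q = 0.10 and p = 0.30, the result becomes 94.5 of 350 × 0.90 = 315 (30%) in place of 129.5 of 350 (37%). This puts the timing right. It does not isolate an effect of the DEI in a one-group design, and the report should say so.
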